In particular, the first aim will be to assess the short-term and long-term efficacy of tele@cognitive protocol as compared to an unstructured cognitive at-home rehabilitation in the treatment of a cohort of patients with CNDs, monitoring intervention effectiveness by a clinical, functional, neurocognitive, and quality of life assessment applied before treatment (T0), after treatment (5 weeks, T1), and at a 3-month follow up visit (T2). We hypothesize that this digital health at-home intervention would ameliorate cognitive abilities more than unstructured at-home rehabilitation in subjects with SCCs, MCI, and PD. We will also evaluate adherence to the rehabilitation program delivered at-home in the absence of therapist supervision. It is hypothesized that, at an early stage of the disease, cognitive telerehabilitation treatment with innovative digital solutions can bring about positive effects on treatment adherence and difficulties specific to each clinical condition.

The second aim will be to investigate the effects of a cognitive rehabilitative protocol based on a digital health at-home intervention (tele@cognitive) on biomolecular and neurophysiological markers, hypothesizing that people with CNDs enrolled in the tele@cognitive protocol will develop changes in circulating biomarkers and patterns of connectivity. Specifically, at T0 and T1, we will study the effect of tele@cognitive treatment on: i) blood biomarkers reflecting neurodegeneration, amyloid-β, tau and alpha-synuclein pathologies, neuroinflammation, synaptic function, and neuronal communication; ii) neurophysiological responses to TMS over the motor cortex. This approach will give a broad overview of the circuits modulated through telerehabilitation (tele@cognitive treatment), possibly highlighting differential effects between the groups.

Finally, the third aim will be to investigate potential cognitive, neurobiological, and neurophysiological predictors of treatment outcomes in people with CNDs who received innovative technology-enhanced telerehabilitation intervention (tele@cognitive group).

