### 2.5. Intervention Procedures

The cognitive rehabilitation protocol (5 weeks, 3 sessions/week, 45 min/session) will be delivered to all participants according to the corresponding experimental group:-30 CNDs patients will receive home-based cognitive rehabilitation activities with an innovative digital solution for remote rehabilitation of cognitive difficulties (tele@cognitive group);-30 CNDs patients will receive home-based unstructured cognitive rehabilitation treatment (Active Control Group—ACG).

The technological solution that will be applied in the tele@cognitive group consists of: (a) a telemedicine platform (RICORDO platform), which allows prescription and planning of digital content for cognitive rehabilitation and monitoring of the rehabilitation cycle and (b) RICORDO application [http://www.ricordo-dtx.com/ (accessed on 10 January 2025)] that will be downloaded on tablets provided to patients by the recruiting units, which will allow the patient to benefit from personalized rehabilitation treatment remotely and in asynchronous mode. In detail, through RICORDO platform, the clinician will have the possibility of prescribing, within the patient’s Individual Rehabilitation Plan (PRI), a personalized intervention that will involve the use of libraries of digital rehabilitation content that maps all the neurocognitive domains provided for in the most recent version of the Diagnostic and Statistical Manual of Mental Disorders (DSM-5) [102]. In particular, the rehabilitation program will include cognitive activities focused on cognitive domains, such as executive functions, memory (long-term memory of both verbal and visuospatial type, autobiographical memory, and semantic memory), attention (selective attention and divided attention), and spatial–temporal orientation and language. Each cognitive exercise will be structured into five levels of difficulty that adaptively increase (algorithms on both subject’s performance and perceived difficulty). All data on patient progress and adherence will be collected and will be available to evaluate and monitor the results of rehabilitation.

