Data will be preprocessed to clean and normalize them appropriately. These will include handling missing values (e.g., using imputation for continuous variables and mode replacement for categorical variables), standardizing features to a common scale, and encoding categorical variables as needed. Machine learning algorithms, such as random forests, support vector machines, naive bayes classifiers, and ensemble techniques, will be applied to develop predictive models for treatment outcomes using the collected information [123]. Model performance will be assessed using cross-validation techniques like leave-one-out or Kfold, and parameters will be fine-tuned using grid search techniques to optimize model performance [124]. To ensure generalizability, performance will also be evaluated using metrics such as accuracy, precision, recall, and area under the ROC curve (AUC-ROC), depending on the nature of the prediction task.

For tasks involving high-dimensional or complex data, such as neurophysiological signals or time-series patterns, deep learning architectures (e.g., convolutional neural networks for spatial data, recurrent neural networks for temporal data) will be employed. These models will be customized and optimized using grid search to ensure they are well-suited to the specific characteristics of the data.

After model training, explainable AI (XAI) techniques, such as SHAP (Shapley Additive exPlanations) values will be employed to interpret the model’s predictions and quantify the contribution of each feature to the outcome [125]. SHAP values provide a unified measure of feature importance by assessing the impact of individual features on the model’s output, not only enhancing the clinical interpretability and transparency of the predictive models but also providing insights into which factors are most influential in driving treatment outcomes.

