In this context, our telerehabilitation protocol represents an ideal solution to provide intensive, long-lasting cognitive rehabilitation and to sustain treatment adherence, as well as to modify daily care routines. We expect that the findings of the present RCT will result in a recommendation of the use of a usable, safe, and effective way for changing CNDs’ behavior patterns, triggering mechanisms at the neurophysiological and neurobiological levels. The added value of this trial consists of: (i) adopting an asynchronous model of care out of the clinic, bypassing typical barriers obstructing accessibility to care structures and lowering system overburdening and costs; (ii) investigating the potential neurobiological and neurophysiological markers of the effects of the at-home tele@cognitive treatment; (iii) investigating potential cognitive, neurobiological, and neurophysiological predictors of response to the treatment, helping in the development of useful treatment pathways for patients with CNDs. It is necessary to clarify which types of patients can benefit the most from rehabilitation interventions and, above all, to pursue a more precise characterization of the specific intervention procedures. However, we acknowledge that the present RCT study has some limitations. In particular: a larger sample size might allow us to account for individual differences that could influence the efficacy of the treatment; we have not planned a cost-effective analysis of the telerehabilitation approach [168]; longer follow-up visits should be useful in following the progress of the improvement obtained after treatment. Moreover, it would have been useful to administer a scale that measured subjective experience and the attractiveness (hedonic quality) of the technology (e.g., UEQ scale; [169,170]).

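### Section 2.8 commits to deep networks for neurophysiological signals, but aim 3 has at most 30 treated patients: too few to tune such models reliably or show that they beat a simple one

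*Protocol article*

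**What the plan says.** Section 2.8 (Statistical Analysis) first lists conventional machine-learning algorithms for the predictive modelling. Of these it says: "Model performance will be assessed using cross-validation techniques like leave-one-out or Kfold". A separate paragraph then adds deep learning. It opens "For tasks involving high-dimensional or complex data, such as neurophysiological signals or time-series patterns, deep learning architectures" and gives as examples "convolutional neural networks for spatial data, recurrent neural networks for temporal data) will be employed". On tuning it says: "These models will be customized and optimized using grid search to ensure they are well-suited to the specific characteristics of the data". The paragraph after that applies SHAP values to the trained models to rank the factors that drive outcome.

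The third aim in section 1 restricts the prediction question to "people with CNDs who received innovative technology-enhanced telerehabilitation intervention (tele@cognitive group". Section 2.5 gives the size of that group: "30 CNDs patients will receive home-based cognitive rehabilitation activities with an innovative digital solution". Section 2.3 confirms 30 per group and says that this already allows for drop-out, without giving a rate.

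Sections 2.6.3 and 2.7 define the TMS quantities: resting motor threshold (rMT), motor-evoked potential (MEP) amplitude and latency, short-interval intracortical inhibition (SICI) at four intervals and short-latency afferent inhibition (SAI) at four intervals. Section 3 acknowledges that "a larger sample size might allow us to account for individual differences that could influence the efficacy of the treatment".

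**The concern.** The number of independent outcomes in aim 3 is the number of treated patients, however many pulses or sessions each one contributes. A network with more weights than patients can reproduce any set of labels, so its fit to the training data says nothing. Grid search does not add information. It chooses among networks using the same 30 or fewer outcomes, so it cannot ensure that any of them suits the data.

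The consequence reaches past poor accuracy, because section 2.8 goes on to interpret the fitted models through SHAP. If a network has memorised its labels, the ranking of its inputs may be a ranking of noise. Sections 3 and 4 hope that the predictors found will shape later treatment pathways.

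**Working it through.** **1. Patients available.** Inputs from section 2.3: d = 0.784, two-sided alpha 0.05, power 0.80 (printed there as beta), 1:1 allocation.

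- Normal approximation: n per arm = 2(1.960 + 0.842)² / 0.784² = 15.70 / 0.6147 = 25.5, so 26.
- Two-sample t-test: 26.53, so 27 per arm.
- With an assumed drop-out of 10%: 27 / 0.90 = 30 per arm, 60 in total.

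The article's figure of 60 is reproduced. Aim 3 therefore has 30 patients at most, and about 27 if 10% drop out.

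**2. Weights in small networks.** The article gives no architecture, so these are illustrative.

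| Network | Weights | Per patient (÷ 30) |
|---|---|---|
| Recurrent (GRU), 4 units, one input | 3(4 + 16 + 8) + 5 = 89 | 3 |
| Recurrent (GRU), 16 units, one input | 3(16 + 256 + 32) + 17 = 929 | 31 |
| Convolutional, two small layers | 80 + 656 + 272 + 17 = 1,025 | 34 |
| Convolutional, one layer plus 16-unit dense layer | 160 + 1,792 + 16 + 17 = 1,985 | 66 |

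Even the smallest has about three weights per patient.

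**3. Fit and prediction.** Simulation with 30 training patients, 1,500 new patients and 60 replicates per scenario. The 1,985-weight network on assumed MEP-like waveforms was compared with a ridge logistic model on TMS-type summaries. The full set has 1 (rMT) + 2 (MEP) + 4 (SICI) + 4 (SAI) = 11 summaries; a two-summary set (amplitude and latency) was also tried.

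| Assumed truth | Network, training accuracy | Network, AUC in new patients | 2 summaries | 11 summaries |
|---|---|---|---|---|
| No signal | 100% | 0.50 | 0.50 | 0.50 |
| Signal in MEP amplitude | 100% | 0.62 | 0.74 | 0.64 to 0.66 |
| Signal only in waveform shape | 100% | 0.68 | 0.50 | 0.50 |

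The training fit was perfect in every replicate of every scenario, and mild weight decay did not change that. With signal in amplitude, the network did worse than two summaries in 100% of replicates and worse than eleven in 70% to 75%. With signal only in waveform shape, it did worse in 0% to 3%.

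**4. Precision with 30 outcomes.** Hanley–McNeil: Var = [A(1 − A) + (n₁ − 1)(Q₁ − A²) + (n₂ − 1)(Q₂ − A²)] / (n₁n₂), with Q₁ = A/(2 − A) and Q₂ = 2A²/(1 + A).

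For A = 0.70 and n₁ = n₂ = 15: Q₁ = 0.538, Q₂ = 0.576, Var = (0.210 + 0.678 + 1.211) / 225 = 0.00933, SE = 0.097. The 95% interval is 0.70 ± 1.96 × 0.097, about 0.51 to 0.89. The even split is an assumption. A 13 v 14 split gives SE 0.103 (0.50 to 0.90), and 10 v 20 gives SE 0.107 (0.49 to 0.91).

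Two models judged on the same patients have correlated AUCs. The SE of their difference is about 0.097 × √(2(1 − r)): 0.097 if r = 0.5 and 0.061 if r = 0.8 (r is assumed). The observed gap would have to reach about 0.12 to 0.19 before its 95% interval excluded zero. Smaller differences between candidate networks on a tuning grid could not be told apart.

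**The case against.** Five points can be made for the plan.

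- **Prediction.** A reader might infer that networks would predict new patients worse than the TMS summaries. The documents do not support that as a general statement. It holds if the signal lies in amplitude, shrinks to 0.02 to 0.04 in AUC when all 11 summaries are entered, and reverses if the signal lies in waveform shape. The article does not say which case applies. The simulated network was also not grid-searched. This objection stands, and the point does not rest on worse prediction.
- **Cross-validation.** A perfect training fit would be exposed by cross-validation, which section 2.8 plans for its machine-learning models. That is right as far as accuracy goes. It does not solve tuning and comparison on 30 outcomes, or make the SHAP rankings trustworthy.
- **Leakage.** A reader might fear that pulses or sessions of one patient would fall in both training and test folds. No section says that records will be split in this way, and with one row per patient leave-one-out means leaving out a patient. This is not a fault of the text; splitting by patient is a free safeguard.
- **Conditional and additional.** The deep-learning sentence is conditional, the architectures are examples, and the neurophysiological parameters enter the other algorithms anyway. All true, but the condition names this trial's own neurophysiological signals, so the commitment remains.
- **Pilot.** The study is a pilot looking for potential predictors, and the primary outcomes are untouched. This limits the stakes and supports relabelling the analysis over removing it.

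**Conclusion.** The point holds in a limited form. The article states an analysis that its own sample cannot support: networks with 89 to about 2,000 weights for at most 30 patients, tuned by a search said to ensure suitability. The simulated network fitted random outcomes perfectly. At this size an AUC of 0.70 is known only to within about ±0.19, so neither reliable tuning nor a demonstrated advantage over a simple model can be expected unless the true gap is large. SHAP rankings from such models may reflect noise.

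The cap of 30 comes from the article. The weight counts rest on illustrative architectures, the AUCs on assumed waveforms and effect sizes, and the interval on an assumed even split of responders. The point affects aim 3 only.

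**What to change.** In section 2.8, and in the analysis plan:

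- Name a penalised regression on the TMS summaries already defined (rMT, MEP amplitude and latency, SICI, SAI) as the main model for neurophysiological predictors. The other planned algorithms can stay. If SICI or SAI is reduced to fewer values than the four intervals, state the rule beforehand.
- Label any convolutional or recurrent network analysis exploratory. Report it only beside that benchmark, with tuning nested inside cross-validation and every fold split by patient.
- Draw no predictor or SHAP conclusions from a network unless it beats the benchmark.
- Remove the claim that grid search ensures the models suit the data.

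The cost is a change of wording and the work of nested tuning; no data are lost, and the raw signals remain available for a larger study. The downside is that waveform patterns beyond the summaries would be reported only as hypothesis-generating, even if that is where the signal lies.

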### 2.2. Randomization and Blinding

The assigned group will be obtained by stratified randomization (1:1 ratio), according to clinical condition, age, and his/her performance in the Montreal Cognitive Assessment (MoCA) test [94,95,96]. Stratified randomization will be achieved by generating a separate block for each combination of covariates, and participants will be assigned to the appropriate block of covariates by a researcher blinded to the study’s aims. Details of the allocated group will be given on cards contained in sequentially numbered, opaque, and sealed envelopes. A blinded researcher will conduct the evaluations.

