### 2.3. Sample Size

In the RCT, patients will be assigned to either receive tele@cognitive protocol or a home-based unstructured cognitive stimulation (ACG). The sample size of the present study was estimated on the basis of a previous work on people within the Alzheimer’s Disease continuum [3] and it was computed on a primary outcome variable (an increase in MoCA score). Applying a two-tailed independent samples *t*-test (alpha = 0.05, beta = 0.80) and considering the effect size (d = 0.784) between two types of intervention (tele@cognitive vs. ACG), we obtained a minimum sample size of 60 subjects (30 per group), taking into account the drop-out rate.

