## 4. Conclusions

At present, pharmacological therapies to prevent cognitive decline have not had great success and, consequently, much emphasis has been placed on non-pharmacological cognitive intervention to stimulate cognitive abilities and prevent functional decline.

EARLY-COGN^3 project could lead to a complete paradigm shift from the traditional therapeutic approach, forcing a reassessment on how CNDs could take advantage of a digital solution. Being software-based, our telerehabilitation protocol will allow clinicians to remotely collect data on patient progress and adherence, allowing a better customization of the rehabilitation program. Our telerehabilitation protocol would give the opportunity to target the need for rehabilitation of CNDs, which is poorly addressed by the healthcare system. We expect that this intervention will induce long-lasting positive effects. Moreover, this study will achieve its aim to elucidate the neurophysiological and biochemical mechanisms of this innovative intervention, and this knowledge will constitute a step forward in the development of effective telerehabilitation interventions. EARLY-COGN^3 could highlight potential predictors of treatment response, paving the way to more efficacious treatment pathways.

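### Section 2.8 reads SHAP values as contributions to patients' outcomes without tying that reading to whether the model predicts; with at most 30 patients and about 55 features, noise alone yields an apparent leading factor

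*Protocol article*

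**What the plan says.** The Introduction limits Aim 3 to people who received the tele@cognitive programme; section 2.5 puts 30 patients in that group.

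Section 2.8 describes the modelling in this order:

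- Features are screened, with chi-square tests and mutual information named as examples. No significance level is given, and nothing is said about what follows if no feature passes.
- Several kinds of classifier are fitted and tuned by grid search.
- Performance is assessed by cross-validation, with metrics such as accuracy and AUC.
- Once models are trained, SHAP values are used to "quantify the contribution of each feature to the outcome".

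The closing sentence of section 2.8 first describes SHAP as measuring how each feature affects what the model puts out. It then says that this provides "insights into which factors are most influential in driving treatment outcomes". The Conclusions add: "EARLY-COGN^3 could highlight potential predictors of treatment response, paving the way to more efficacious treatment pathways".

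**The concern.** Two different quantities are treated as one. A feature's effect on a model's prediction is a fact about the fitted model. A feature's contribution to the patient's outcome is a claim about patients. The first supports the second only to the extent that the model predicts outcomes in patients it has not seen. Section 2.8 plans to measure that ability but does not make the SHAP reading depend on it.

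This is separate from optimism in a reported AUC. Even if validation were done perfectly and showed no predictive ability, the text as written would not stop the SHAP values from being read as influential factors. At stake is the output of one of the trial's three aims: features that lead by chance could be carried forward as candidate predictors of response.

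**Working it through.** **1. The only design figure in the article.** Section 2.3 gives a "two-tailed independent samples" t-test with "alpha = 0.05, beta = 0.80" (0.80 read as power) and "considering the effect size (d = 0.784". Allocation is 1:1 (section 2.2).

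- Normal approximation: 2 × (1.960 + 0.842)² / 0.784² = 25.5, so 26 per group.
- Exact t-test: 26.53, so 27 per group.
- With an assumed 10% drop-out: 27 / 0.90 = 30 per group, 60 in all.

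This agrees with the stated "minimum sample size of 60 subjects (30 per group), taking into account the drop-out rate". The figure concerns the MoCA comparison; nothing comparable is stated for Aim 3.

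**2. Size of the Aim 3 problem.** Patients: at most 30, or 27 after the assumed 10% drop-out. Candidate baseline features, counted from sections 2.6 and 2.7:

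- Clinical and cognitive, 28: MoCA 1, FCSRT 5, EQ-5D-3L 6, MDS-UPDRS 2, HDRS 1, STAI-Y 2, NPI 1, EMQ 1, CPM 1, TMT 2, Stroop 2, ROCF copy and recall 2, verbal fluency 2.
- Biomolecular, 16: 13 analytes, plus vesicle concentration, size and their ratio.
- TMS, 11: rMT 1, MEP amplitude and latency 2, SICI at 4 intervals, SAI at 4 intervals.

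Total 28 + 16 + 11 = 55. This is a count, not a figure from the article, so 20 to 60 was used as the range.

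**3. What SHAP decomposes.** For a linear model with independent features, the SHAP value of feature j in patient i is b_j × (x_ij − mean_j). Summed over features, this gives the patient's prediction minus the average prediction. The outcome enters only through the fitted coefficients b_j. If these are fitted to noise, the SHAP values describe noise.

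**4. Null simulation.** Assumptions: independent Gaussian features, a balanced binary outcome unrelated to any of them, ridge model with penalty 10, importance = mean |SHAP|, stratified 5-fold cross-validation, 1,000 runs per setting.

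| Patients | Features | Top / median importance | Apparent AUC | Mean cross-validated AUC |
|---|---|---|---|---|
| 30 | 20 | 3.49 | 0.955 | 0.504 |
| 30 | 40 | 3.90 | 1.000 | 0.500 |
| 30 | 60 | 4.26 | 1.000 | 0.497 |
| 27 | 60 | 4.32 | 1.000 | 0.506 |
| 60 | 60 | 3.97 | 0.999 | 0.496 |

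At 30 patients and 55 features, one set of 400 runs gave a ratio of 4.2. A separate run gave 3.8, with a mean cross-validated AUC of 0.49. A heavier penalty (30) with R² as the metric gave 3.3 for 20 features and 3.8 for 60. A random forest check (30 patients, 55 features, 100 runs) gave 4.3, but used impurity importance because no SHAP package was available.

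**5. The feature screen, read as a 0.05 test per feature.** P(at least one false predictor) = 1 − 0.95^p under independence: 0.64 for p = 20, 0.87 for p = 40, 0.94 for p = 55. The expected number of false predictors at p = 55 is 55 × 0.05 = 2.75.

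**6. Where selection is done.** If five features are picked on all 30 patients before cross-validation, the null AUC averages 0.73, 0.80 and 0.83 for 20, 40 and 60 features. Performance would then look real when it is not.

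**7. The remedy tested.** With 30 patients, 55 features and no true predictor, SHAP was read only if cross-validated AUC passed a 5% permutation test (99 permutations). Readings went ahead in 5.75% of 400 runs, close to the nominal 5%. A plain requirement of AUC at or above 0.70 still let through 11%.

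**The case against.** The strongest reply is that this is an omission from a condensed article. A performance condition could stand in a full protocol or analysis plan that is not shown, and a point resting only on its absence would fail. That is right as far as it goes. But the article itself states that SHAP quantifies contribution to the outcome and shows what drives it. That statement is wrong as published, whatever another document adds.

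Other parts of the reply also have force:

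- **Certainty of a false result.** A reader might infer that the plan is certain to declare predictors even when none exist. The text does not support that. It sets no ranking cut-off and no rule by which top-ranked features are declared predictors. Any list of unequal numbers has a largest member, so that certainty is a property of ranking, not of this trial.
- **Existing safeguards.** The screen and the cross-validation come before SHAP in the text, and investigators who saw an AUC near 0.5 might well stop. In the R² simulations, cross-validated R² was at or below zero in about 85% of null runs, so honest validation would often show the problem. The protection is informal, however, and the article does not say whether selection is kept inside the folds.
- **Modest claims elsewhere.** The trial is a pilot, and the article speaks of potential predictors that it could highlight. To say that Aim 3 cannot be answered would go too far.
- **The simulation is not the plan.** It omits tuning and selection inside the folds, and takes features as independent. The ratios are illustrative.

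**Conclusion.** The point holds as one about wording and about a missing link between two planned steps. Section 2.8 equates contribution to a model's output with contribution to the outcome, and starts the SHAP reading from training, not from shown predictive ability.

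At Aim 3's size, a model with no skill still presents an apparent leader at roughly 3.5 to 4 times the median importance (3.3 to 4.3 over all settings tried). The screen would not reliably prevent this even if run at 0.05. These sizes rest on the feature count, independent features, a balanced binary response and, in the main, a ridge model. The mismatch between model output and outcome rests on none of them.

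The change is worth making before outcome data are modelled. It does not touch the primary or secondary efficacy comparisons.

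**What to change.** In section 2.8 and in any analysis plan:

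1. Run feature selection and tuning inside the cross-validation folds.
2. Repeat the whole pipeline on permuted outcomes. Interpret SHAP only if the real out-of-fold performance exceeds a stated point of that permutation distribution, for example its 95th percentile. Otherwise report that no predictor was identified.
3. Replace "quantify the contribution of each feature to the outcome" and the claim about factors that drive outcomes with wording that refers to contribution to the model's prediction, and label the result exploratory.

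A further per-feature threshold, such as the permutation distribution of the largest mean |SHAP|, is optional; it is one reasonable standard among several.

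The cost is text and computing time, with no new patients or data. The downside is that Aim 3 may end with no predictor reported.
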